## Methods/design

### Study aim and design

The PREP study is a prospective, double-blinded, placebo-controlled, randomized trial ongoing at Asan Medical Center, Seoul, Korea. The primary aim of the study is to investigate the efficacy of probiotics, starting 2 weeks before radiotherapy, to prevent acute RIE in patients being treated with pelvic radiotherapy for gynecologic or urologic malignancies. Secondary aims include evaluations of the effects of probiotics on the incidence of chronic RIE and the safety of probiotics in patients with gynecologic or urologic cancer.

The design of the PREP trial is illustrated in Fig. 1. Patients diagnosed with gynecologic or urologic malignancies and scheduled to undergo pelvic radiotherapy will be screened and provided with an appropriate explanation about the PREP trial. Written informed consent will be obtained by radiation oncologists from patients who elect to participate in the study. After stratification by sex, participants will be randomly assigned 1:1 to the probiotics or placebo group using blocked randomization. Sex will be the single stratification factor, as patients with gynecologic malignancies have a greater tendency to require concurrent chemoradiotherapy, which affects the incidence of RIE. The block size and sequence for randomization will vary. The randomization sequence will be generated by a central web-based computer so that allocation will be concealed from the primary investigator who enrolls the patients. Neither participants nor physicians will be aware of their group assignments.

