### Sample size and statistical analysis

Two proportion test in Power Analysis and Sample Size Software 2018 (NCSS, LLC. Kaysville, Utah, USA) was utilized to estimate the sample size. Based on the assumption that 30% of the patients in the placebo group and 15% of the patients in the probiotics group will experience grade ≥ 2 acute toxicities, 118 patients per group will be required to show a significant effect based on an alpha value of 0.05 and a beta of 0.2. Assuming a 5% dropout rate, 124 patients per group will be required (total, 248 patients).

Acute toxicities will be analyzed in the intention to treat population, with categorical variables in the two groups compared by the Chi-Square or Fisher’s exact test. To find the other confounding factors for RIE, univariate and multivariate logistic regression for acute toxicity will be performed. The times from the start of radiotherapy to acute grade ≥ 2 toxicities and to any chronic toxicities will be calculated using the Kaplan-Meier method and compared in the two groups using the log-rank test to compare survival curves between two groups. In the whole population, multivariate analysis, Cox proportional hazard model will be utilized to find the significant factor for the incidence of RIE in addition to the use of probiotics. Factors with *p* ≤ 0.2 in log-rank test will be entered in multivariate analysis. Descriptive statistics of all analyzed parameters will be provided, whenever appropriate.

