The largest prospective double-blind, placebo-controlled trial performed to date on the relationship between probiotics and RIE [6] found that the incidence of radiation induced diarrhea was significantly lower in the probiotics than in the placebo group (31.6% vs. 51.8%, *P* < 0.001), as was the incidence of grade 3 or 4 diarrhea (1.4% vs. 55.4%, *P* < 0.001). That study, however, did not provide information on chemotherapy, one of the major factors contributing to RIE, nor did it evaluate the incidence of chronic RIE. Furthermore, IMRT is frequently utilized in real-world clinical conditions for pelvic radiotherapy, suggesting the need to evaluate the effects of probiotics in patients undergoing IMRT.

Probiotics are generally considered safe in a healthy population [20]. However, it is essential to investigate the safety of probiotics in immunocompromised cancer patients. Case studies have reported that the probiotics Lactobacillus and Bacillus may cause infection in these patients, resulting in sepsis [26, 27]. However, a systematic review of the use of probiotics in cancer patients demonstrated that sepsis due to probiotics was rare [28]. The inclusion criteria of the PREP trial will filter out severely immunocompromised patients. Moreover, the strain of *Bacillus licheniformis* that will be used in the PREP trial has never shown toxicity in humans, but has reduced the incidence of diarrhea associated with antibiotic therapy [29]. One in vivo study suggested that this probiotic may carry a risk of antibiotic resistance [30].

The purpose of the PREP study is to provide high-level evidence on the use of probiotics for reducing the incidence of RIE. We anticipate that the rate of acute RIE will be significantly lower in the probiotic than in the placebo arm. We also expect that probiotics will decrease the incidence of chronic RIE and will have little or no toxicity in these patients.

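### The secondary Cox model admits covariates by a log-rank p ≤ 0.2 screen, so chemotherapy and the stratifier, sex, can be lost by chance

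*Protocol article*

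**What the plan says.** All statements are in the protocol article.

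- **Entry rule (Sample size and statistical analysis).** Factors with p ≤ 0.2 "in log-rank test will be entered in multivariate analysis". No covariate is named as always retained.
- **Purpose of the model (same section).** "Cox proportional hazard model will be utilized to find the significant factor for the incidence of RIE in addition to the use of probiotics".
- **Logistic model (same section).** "To find the other confounding factors for RIE, univariate and multivariate logistic regression for acute toxicity will be performed". No entry rule is given for it.
- **Main comparison (same section).** "Acute toxicities will be analyzed in the intention to treat population", by Chi-square or Fisher's exact test. Time to toxicity is compared between groups by log-rank test. Neither analysis uses covariates.
- **Stratification (Study aim and design).** "Sex will be the single stratification factor". The reason given is that gynecologic patients have a "greater tendency to require concurrent chemoradiotherapy, which affects the incidence of RIE".
- **Chemotherapy (Discussion).** The largest earlier trial is criticised because it "did not provide information on chemotherapy, one of the major factors contributing to RIE".

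**The concern.** The article says in advance that chemotherapy matters for enteropathy, and it stratifies on sex because sex tracks chemoradiotherapy. It then lets a univariable p-value decide whether either enters the multivariable model. With few events, such a screen is noisy in both directions: real factors of moderate strength are missed, and noise factors get in. The p-values from the final model are read as if its contents had been fixed beforehand.

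What is at stake is the model's own stated output, the list of factors associated with enteropathy, together with proper adjustment for the stratifier. A trial that faults an earlier one for silence on chemotherapy could itself publish a multivariable model without chemotherapy because its log-rank p happened to exceed 0.2.

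**Working it through.** **1. The plan's own sample size.** Inputs from Sample size and statistical analysis: 30% and 15% with grade ≥ 2 acute toxicity, alpha 0.05 (taken as two-sided), power 0.80. With unpooled variance:

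n = (1.960 + 0.842)² × (0.30×0.70 + 0.15×0.85) / 0.15² = 117.7, so 118 per group, as stated. For 5% dropout, 118 × 1.05 = 123.9, so 124 per group and 248 in total, as stated.

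**2. Events available to the screen.** 118 × (0.30 + 0.15) = 53.1, or 124 × 0.45 = 55.8 if all enrolled patients contribute. This gives 53 to 56 acute events. The article gives no event rate for chronic toxicity, so nothing is computed for it.

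**3. Chance that a real factor is dropped.** For a binary factor with prevalence a, hazard ratio HR and D events, the log-rank statistic is approximately normal with variance 1 and mean (Schoenfeld)

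θ = √(D·a·(1−a)) × ln(HR).

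The factor is dropped when |Z| < 1.2816, the two-sided 0.2 cut-off, so P(drop) = Φ(1.2816 − θ) − Φ(−1.2816 − θ).

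Worked cases at D = 53, a = 0.5:
- HR 1.5: θ = 3.640 × 0.405 = 1.476, P(drop) = 0.42.
- HR 2.0: θ = 3.640 × 0.693 = 2.523, P(drop) = 0.107.

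HR and prevalence are assumptions, so both were varied. Each cell shows the percentage dropped with 53 / 56 events:

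| HR | prevalence 50% | prevalence 30% | prevalence 20% |
|---|---|---|---|
| 1.3 | 61.5 / 60.6 | 64.2 / 63.4 | 67.7 / 67.1 |
| 1.5 | 42.0 / 40.4 | 46.7 / 45.3 | 53.3 / 52.1 |
| 2.0 | 10.7 / 9.5 | 15.1 / 13.7 | 23.0 / 21.3 |
| 2.5 | 2.0 / 1.6 | 3.8 / 3.1 | 8.3 / 7.2 |
| 3.0 | 0.3 / 0.2 | 0.9 / 0.6 | 2.8 / 2.2 |

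A simulation (248 patients, 600 runs per scenario, prevalence 30% and 50%) agrees: 62–64% dropped at HR 1.3, 39–42% at 1.5, 9–12% at 2.0 and under 1% at 3.0.

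**4. Noise factors.** A factor with no effect passes with probability 0.20. Given that it has passed, its univariable p-value is roughly uniform between 0 and 0.2, so it lies below 0.05 with probability about 0.05 / 0.20 = 25%. If the multivariable p-value stays close to the univariable one, a null factor in the final model appears significant about one time in four, not one in twenty.

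**5. Effect on the treatment estimate.** In the same simulation, the mean absolute difference between adjusted and unadjusted treatment log hazard ratios was 0.015–0.065. The largest shift when the factor was dropped was about 0.10. The standard deviation of the estimate was about 0.28–0.31. At HR 2.0 and prevalence 30%, the average treatment hazard ratio was 0.447 with the factor forced in and 0.448 with screening.

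**The case against.** The strongest reply is that nothing decisive rests on this model. The intention-to-treat test and the log-rank comparison of the groups are unadjusted, and the Cox model is a secondary search for factors. That is correct. A reader might infer from the screen that the probiotic effect itself is at risk. The documents do not support this: no adjusted effect is named for inference, and step 5 shows that randomisation keeps the shift small.

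Other stronger readings also fail:

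- **Treatment must itself pass the screen.** The sentence before the entry rule seeks factors additional to probiotics, which implies that treatment is already in the model.
- **Several major factors are at risk, including bowel dose.** Only chemotherapy is called major. Sex is there because it tracks chemoradiotherapy. Bowel dose appears as a planning constraint and in text on mechanism, not as a named covariate.
- **The logistic model is screened too.** The rule is written for log-rank p-values, and no rule is stated for the logistic model.
- **Continuous factors will be cut into groups.** The article does not say how they are handled, and that detail may stand in a fuller document.

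It is also fair that a very strong factor is seldom lost (2–8% at HR 2.5, at most 3% at HR 3.0), and that passing the screen is not the same as being declared significant.

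The reply that a condensed article may leave covariate detail to the full protocol does not dispose of the point. The article states the selection method outright and gives no exception.

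**Conclusion.** The point holds as a modest one about a secondary analysis. On the planned 53 to 56 acute events, the p ≤ 0.2 rule drops a real factor of moderate strength in about 40–53% of trials at HR 1.5 and 10–23% at HR 2.0, and it admits each noise factor 20% of the time. These figures assume a binary factor with prevalence 20–50%, proportional hazards and the planned event rates. If chemotherapy is very strong in this population, the risk of losing it is small. The damage falls on the risk-factor list, its p-values and adjustment for sex. The trial's primary conclusion and its type I error are not affected.

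**What to change.** Replace the entry rule with a statement to this effect: the Cox model always contains treatment, sex and concurrent chemotherapy, whatever their p-values; the multivariable logistic model contains the same three terms; any further factor, however chosen, is reported as exploratory. Make the change before unblinding.

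Three terms on 53 events leave 53 / 3 ≈ 18 events per term, so the model is supportable and the sample size stays as it is.

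There are two costs. Sex and chemotherapy are expected to be correlated, so their separate coefficients will be less precise and should be read with that in mind. Chemotherapy status must be taken from treatment records, because the data collection section mentions only endpoint data. Defining it as planned at randomisation would keep it a baseline variable.

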## Discussion

Radiotherapy is utilized in about 50% of cancer patients [1], and its role is especially crucial in patients with gynecologic and genitourinary malignancies. Radiation is required to manage 80–90% of women with carcinoma cervix, 60% of women with endometrial cancer, and 50% of women with carcinoma vulva [14]. Radiotherapy is a major treatment option for every stage of prostate cancer [15] and has been adapted for bladder cancer patients who want bladder preservation [16]. However, 60–80% of patients who receive pelvic radiotherapy experience acute RIE [1], which may lead to late RIE and affect the quality of life of long-term cancer survivors. The Post Operative Radiation Therapy in Endometrial Cancer (PORTEC-2) trial demonstrated that diarrhea was significantly more frequent in patients who did than did not receive pelvic radiotherapy, indicating that treated patients must remain close to a toilet, reducing their social functioning and quality of life [17]. Although high precision radiotherapy techniques such as IMRT have been widely introduced to reduce irradiation of the bowels, about 50% of patients who received pelvic IMRT experience acute gastrointestinal toxicities of any grade [18], and 34% of patients suffer from frequent or almost constant severe diarrhea [19].

Several studies have evaluated the usefulness of probiotics in patients with infectious diarrhea and antibiotic-induced diarrhea [20]. Probiotics are also used to control inflammatory bowel disease (IBD) as gut dysbiosis is regarded as having a potential pathogenic role in IBD [21]. Although the precise mechanisms by which probiotics affect pathogenic situations remain unclear, several hypotheses have been suggested, including restoration of microbial balance, modulation of mucosal protection, protection against pathogens including protective immune responses through immunization, and modification of gut-associated lymphoid cells [22]. Irradiation of the bowels induces cell death in the rapidly proliferating crypt epithelium and protracted acute inflammatory reactions in the lamina propria. Crypt cell death leads to lack of replacement of the villus epithelium, breakdown of the mucosal barrier, and mucosal inflammation [1]. Probiotics have also shown potential in relieving gastrointestinal inflammation in IBS patients during and after radiotherapy [10].

Most studies evaluating the effects of probiotics for RIE have reported that probiotics reduce acute diarrhea [5, 6, 23–25] (Table 1). Most of these studies, however, included small numbers of patients, and only one study started patients on probiotics 1 week before the start of radiotherapy. The beneficial effects of probiotics are thought to be proportional to the concentration of live bacteria [25], but less is known about the optimal period to take probiotics that results in a sufficient concentration of live bacteria. However, probiotics may be less effective when started at the initiation of radiotherapy than beforehand. Thus, the present PREP study is designed so that probiotics will be administered 2 weeks prior to the initiation of radiotherapy.

**Table 1 Tab1:** Characteristics of previous randomized controlled trials studying the effects of probiotics on radiation induced enteropathy

First author	Year /Country	No. of patients Pl/Pr	Primary tumor	Total RT dose (Gy)	Radiation technique	Chemotherapy Pl/Pr (%)	Probiotics	Daily CFU	Timing	Toxicity scoring system	Acute diarrhea (%) Pl/Pr
Linn	2018/ Myanmar	28/26	Cervical	50	2D	79/73	Lactobacillus, Bifidobacterium	6 × 10^9^	During RT, t.i.d.	CTCAE 4.0	Mild–moderate 82/54 (SS)
Demers	2014/ Canada	86/140	Gynecologic, rectal, prostate	40–50.4	NA	56/54 or 45	Lactobacillus, Bifidobacterium	2.6 × 10^9^ or 3 × 10 ^10^	During RT, b.i.d. or t.i.d.	WHO or CTCAE 3.0	Moderate–severe 83/65 (SS)
Chitapanarux	2010/ Thailand	31/32	Cervical	40–56	2D	100	Lactobacillus, Bifidobacterium	4 × 10^9^	1 week before RT, during RT, b.i.d.	CTCAE 2.0	Grade 2–3 45/9 (SS)
Giralt	2008/ Spain	41/44	Cervical, endometrial	40–50	NA	For cervical cancer	Streptococcus, Lactobacillus	3 × 10^8^	1 week, t.i.d.	CTCAE	Grade ≥ 2 59/68 (NS)
Delia	2007/ Italy	239/243	Sigmoid, rectal, cervical	60–70	NA	NA	Lactobacillus, Bifidobacterium, Streptococcus	1.35 × 10^12^	During RT, t.i.d.	WHO	Any grade 52/32 (SS)

*2D* two-dimensional; *CFU* colony forming units; *CTCAE* Common Terminology Criteria for Adverse Events; *No*. number; *NA* not available; *NS* not significant; *Pl* placebo; *Pr* Probiotics; *RT* radiotherapy; *SS* statistically significant; *WHO* World Health Organization

The largest prospective double-blind, placebo-controlled trial performed to date on the relationship between probiotics and RIE [6] found that the incidence of radiation induced diarrhea was significantly lower in the probiotics than in the placebo group (31.6% vs. 51.8%, *P* < 0.001), as was the incidence of grade 3 or 4 diarrhea (1.4% vs. 55.4%, *P* < 0.001). That study, however, did not provide information on chemotherapy, one of the major factors contributing to RIE, nor did it evaluate the incidence of chronic RIE. Furthermore, IMRT is frequently utilized in real-world clinical conditions for pelvic radiotherapy, suggesting the need to evaluate the effects of probiotics in patients undergoing IMRT.

Probiotics are generally considered safe in a healthy population [20]. However, it is essential to investigate the safety of probiotics in immunocompromised cancer patients. Case studies have reported that the probiotics Lactobacillus and Bacillus may cause infection in these patients, resulting in sepsis [26, 27]. However, a systematic review of the use of probiotics in cancer patients demonstrated that sepsis due to probiotics was rare [28]. The inclusion criteria of the PREP trial will filter out severely immunocompromised patients. Moreover, the strain of *Bacillus licheniformis* that will be used in the PREP trial has never shown toxicity in humans, but has reduced the incidence of diarrhea associated with antibiotic therapy [29]. One in vivo study suggested that this probiotic may carry a risk of antibiotic resistance [30].

The purpose of the PREP study is to provide high-level evidence on the use of probiotics for reducing the incidence of RIE. We anticipate that the rate of acute RIE will be significantly lower in the probiotic than in the placebo arm. We also expect that probiotics will decrease the incidence of chronic RIE and will have little or no toxicity in these patients.

## Trial status

Patient recruitment was started on 1 June 2019 and is currently ongoing based on protocol version 1.6.

Recruitment is expected to be complete by 1 June 2021.

## Data Availability

The datasets analyzed during the current study will be available from the corresponding author on reasonable request.

## Abbreviations

CT: Computed tomography
CTCAE: Common terminology criteria for adverse events
CTV: Clinical target volume
IBD: Inflammatory bowel disease
IMRT: Intensity modulated radiotherapy
PTV: Planning target volume
RIE: Radiation induced enteropathy
WHO: World health organization
